# Cervical spine kinematics after anterior cervical discectomy with or without implantation of a mobile cervical disc prosthesis; an RCT

**DOI:** 10.1186/s12891-015-0479-4

**Published:** 2015-02-21

**Keywords:** Cervical disc arthroplasty, Cervical degenerative disc disease, Fusion, Cervical kinematics, Randomized controlled trial

## Abstract

**Background:**

When surgically treating cervical degenerative disc disease, the most commonly performed procedure is anterior cervical discectomy. This procedure is performed with, or without fusion promoting methods. For both options the rate of fusion is high and there is much debate whether fusion of the treated segment is a contributing factor to accelerated degeneration of adjacent motion segments. In an effort to prevent degeneration of adjacent segments (ASDeg) due to loss of mobility at the operated level, cervical disc arthroplasty (CDA) was introduced. To evaluate the effectiveness of CDA in preventing ASDeg long term studies are necessary. However, prevention of ASDeg is based on the premise that mobile disc prostheses preserve cervical spine motion in a physiological way. In this article the authors describe a short term protocol for a study that aims to investigate whether CDA reaches the intended goal: restoration or preservation of physiological cervical spine motion. To this end, a technique is used to establish the sequence of contributions of cervical motion segments to flexion/extension of the spine.

**Methods:**

24 subjects between 18 and 55 years old, with radicular symptoms due to a herniated disc between C5 and C7, refractory to conservative therapy are randomized to simple discectomy, or CDA. These groups are preceded by a pilot group of three subjects receiving CDA. Fluoroscopic flexion-extension recordings are acquired preoperatively, and at three and 12 months postoperative. At these same time points, patient reported outcomes are collected, and a neurological examination is performed by and independent physician.

**Discussion:**

Studies investigating arthroplasty determine mobility by measuring segmental range of motion (sROM), which gives no information other than presence, and quantity, of mobility. SROM suffer from high variability. The authors therefore chose to use a method previously used in healthy controls, to describe the dynamic process of cervical spine motion in more detail. Determining cervical spine motion patterns has been reported to be more consistent than sROM. If a physiological motion pattern is absent after surgery in the CDA group, prevention of future ASDeg is less likely. Radiological outcomes will be correlated to clinical outcomes.

**Trial Registration:**

NCT00868335

**Electronic supplementary material:**

The online version of this article (doi:10.1186/s12891-015-0479-4) contains supplementary material, which is available to authorized users.

## Background

Cervical degenerative disc disease is defined as complaints due to degenerative changes of the intervertebral disc and the intervertebral disc space. Herniation of the intervertebral disc itself or surrounding osteophytes cause radiculopathy due to compression of a nerve root, leading to pain and/or sensory and/or motor deficit. It can also lead to compression of the spinal cord itself causing myelopathy. Surgery can be considered if there is insufficient relief of symptoms with conservative treatment options, such as physical therapy, non-steroidal anti-inflammatory drugs, or immobilisation. Goal of surgery is relieving radiating arm pain in case of radiculopathy and prevention of progressive neurological deficits in case of myelopathy. The most commonly performed procedure is the anterior cervical discectomy, which is being performed either with, or without fusion promoting methods (called ‘fusion’ and ‘simple discectomy’, respectively). Clinical results of these methods are similarly good. Both methods have a high rate of fusion, up to 80% in simple discectomy, and over 95% in fusion [1-4].

There is much debate whether fusion is a contributing factor to accelerated degeneration of adjacent motion segments (adjacent segment degeneration, ASDeg) or not. When this degeneration causes complaints, it is called adjacent segment disease (ASDis). The annual risk of ASDis is reported to be 2.9% [5]. It is not clear if fusion is in fact the culprit, or if it is just progression of degeneration in an ageing spine [6-9].

In an effort to prevent degeneration of adjacent segments due to loss of mobility at the operated level, cervical disc arthroplasty (CDA) was introduced. In CDA, a mobile disc prosthesis is inserted during surgery to preserve mobility of the operated spinal segment. Short term clinical results for CDA are comparable to fusion, which’s results are comparable to simple discectomy [4,10,11]. Long term studies are necessary to evaluate their effectiveness in preventing ASDis [10,12].

Prevention of ASDis is based on the premise that mobile disc prostheses preserve cervical spine motion in a physiological way. Motion of the cervical spine is commonly measured by means of flexion-extension radiographs, which give information about the segmental range of motion (sROM). It suffers from a high intra- and inter-individual variability, severely limiting its use as a tool for diagnosis and follow-up in the individual patient. The sequence in which motion segments contribute to the movement to maximum extension or flexion in the entire cervical spine has been reported to be a more consistent parameter in healthy controls [13-15]. Therefore, a randomized controlled study to investigate the influence of implanting a mobile disc prosthesis on motion in the cervical spine was designed, using analysis of the sequence of segmental contributions.

Primary objective of the study is to ascertain whether a mobile cervical disc prosthesis restores/preserves the sequence of segmental contributions that is present in healthy controls, in contrast to patients undergoing simple discectomy. Secondary goal is to evaluate the clinical results of CDA with the prosthesis used, compared to simple discectomy, to determine if results are comparable to reported results for this type of surgery.

## Methods

### Subjects

Patients referred to our neurosurgical department who are eligible for surgery will be informed about the study and, if willing to receive further information, are then referred to [name] and/or TB to receive detailed study information and to evaluate eligibility. They then have a minimum of one week before they are contacted to inquire if they have any remaining questions and if they are willing to participate.

We include patients with a radiculopathy due to, MRI confirmed, single level soft disc herniation at the C5-C6 or C6-C7 level, refractory to at least 12 weeks of conservative treatment. They must be able to actively make a full flexion to extension movement. If there is osseous degeneration at the target level a flexion/extension radiograph is made to be certain that the segment is not spontaneously fused, which is defined as cortical bridging or less than 2° segmental range of motion. At the time of conception of the study there was insufficient information about safety in patients with myelopathy; patients with a myelopathy are therefore excluded. Other reasons for exclusion are degenerative changes at more than the target level, prior surgery or radiotherapy to the cervical spine, active infection, or a history of malignancy. Inclusion and exclusion criteria are depicted in Additional file 1: Table S1.

Informed consent will be acquired from all participants. The study has been approved by the local institutional medical ethical committee (Medical Research Ethics Committee Maastricht UMC+, METC 06-1-098) and has been registered on clinicaltrials.gov (NCT00868335).

### Sample size calculation

Sample size calculation is based on the presence or absence of fusion at the operated segment, as the primary outcome is expected to be directly correlated to the presence of fusion. Fusion is defined as < 2° range of motion. At an α set at 0.05, the power (β) of 80% to detect a 40% difference in the amount of patients with < 2° range of motion, the necessary number of participants per group is ten. At a projected loss to follow up of 20% the amount of participants needed is twelve in each group. We also include a pilot group of three patients that will all receive CDA, which will precede the randomised groups, to limit the possible influence of a learning curve. The total number of patients that will be included is therefore 27.

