### Statistical methods

Dichotomous outcome measures (presence of normal sequence of segmental contributions, presence of fusion), and ordinal outcome measures (Odom’s outcome scale) will be analysed using a χ2 analysis. Statistical significance will be defined as P < 0.05 in the χ2 analysis. When the requirements of the χ2 analysis are not met (i.e. less than 5 samples per field) Fisher's exact test will be used. Continuous outcome measures (NDI, VAS, SF36, sROM) will be analysed using an independent samples t-Test, after testing for normality. Statistical significance will be defined as P < 0.05 in the t-Test. If normality is not met, a Mann–Whitney *U* test will be used. All data will be analysed according to the ‘intent-to-treat’ principle, additionally a sensitivity analysis will be performed, based on presence or absence of fusion.

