As in almost all surgical studies, caregivers and X-ray analyses cannot be blinded, and patients report their own outcomes, therewith invoking risk of bias. This is a common weakness in this type of study, as blinding patients in these types of device studies is often regarded as not ethically appropriate, and most of the clinical outcomes are patient-reported outcomes [10]. As a result, many of the outcomes may suffer from bias, although the differences that have been reported so far were usually small [10]. The radiological outcome cannot be blinded completely since the prosthesis is clearly visible in the FFER, and although the motion analysis is performed by image recognition software, these analyses are checked manually to avoid errors. The clinical outcome data are collected by a blinded caregiver; since the patient is not blinded the possibility of the caregiver receiving information about the surgery is therefore present. Sample size is small in this study. However, given the large expected difference in the amount of fusion between the groups, and the consistent findings when analysing sequence of segmental contributions, the authors expect to be able to draw conclusions about the primary outcome. For the secondary outcomes the sample size will be too small. However, the authors’ haven previously shown that clinically relevant differences are not to be expected, and only aim to see if results are in line with those described in literature [10].

The study is industry sponsored, as are most of the RCTs on this subject [10]. This also can lead to bias. The influence of a conflict of interest on outcomes in trials investigating CDA has recently been investigated, which led to the conclusion that while there was no influence on quality of life outcomes, it was associated with lower reported complication rates [12]. In the current study the sponsor has no influence on planning or conducting the study, no influence on data acquisition or analysis, or any aspect of the publication process.

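### Ten patients per group do not give 80% two-sided power for a 40-point difference in fusion under the planned tests, whatever the two fusion rates are

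*Protocol article*

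**What the plan says.** The Sample size calculation section of the protocol article bases the trial's size on fusion at the operated level, because the primary outcome is expected to follow fusion closely. Its inputs are "At an α set at 0.05" and a power of "80% to detect a 40% difference in the amount of patients with" a range of motion below 2°. It concludes that ten per group are needed. It then adds: "At a projected loss to follow up of 20% the amount of participants needed is twelve in each group". The section gives no fusion rate for either arm, no sidedness and no formula.

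The Statistical methods section names the test for dichotomous outcomes: "Statistical significance will be defined as P < 0.05 in the χ2 analysis". Fisher's exact test replaces it when the chi-square requirements fail ("i.e. less than 5 samples per field").

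Two other places bear on the point. The Background gives the only fusion rates in the document: "Both methods have a high rate of fusion, up to 80% in simple discectomy, and over 95% in fusion". The Discussion concedes that the sample is small, but because a large difference in fusion is expected (and because sequence findings are consistent), "the authors expect to be able to draw conclusions about the primary outcome".

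**The concern.** Four figures are tied together: alpha 0.05, 80% power, a 40-point difference and ten per group. With groups this small and a binary outcome, 40 points is only four patients in ten, and the planned tests have little room to detect that.

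The statement is the trial's only quantitative justification for its size, and the Discussion relies on a large fusion difference when it expects a conclusion on the primary outcome. If the power is wrong by a factor of two or three, a reader who sees a non-significant result will give it more weight as evidence of no difference than it deserves. The missing fusion rates are not the complaint, since an article may leave them to the full protocol. The question is whether any rates could make the statement true.

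**Working it through.** **Inputs.** Alpha 0.05, power 80%, difference 40 points, ten per group and 20% loss come from Sample size calculation. The tests come from Statistical methods, and 1:1 allocation from Patient allocation and blinding. Two-sided testing is my reading, because a chi-square test at P < 0.05 is two-sided in its usual form. Fusion rates are not given, so every pair (p, p + 0.40) was scanned for p from 0 to 0.60 in steps of 0.01.

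**Trying to reproduce ten per group.** The usual two-sided pooled formula is

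n = [1.96·√(2·m(1−m)) + 0.8416·√(p₁(1−p₁) + p₂(1−p₂))]² / (p₁−p₂)², with m = (p₁+p₂)/2.

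- 0% vs 40%: 14.5, so 15 per group
- 40% vs 80%: 22.3, so 23
- 30% vs 70%: 23.3, so 24
- With continuity correction the range is 20 to 29.

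Values near ten appear only when one arm has about 0% or 100% fusion. At 0% vs 40% the two-sided arcsine formula gives 9, two-sided unpooled 12 and one-sided unpooled 10. These are approximations at the edge of their validity, so exact power was checked next.

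**Exact power by hand at the most favourable pair, 0% vs 40%, n = 10.** The zero-rate arm always shows 0/10, so power is the chance that the other arm reaches the rejection limit.

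- Fisher, 4/10 vs 0/10: p = 2·C(10,4)/C(20,4) = 2·210/4845 = 0.087, not significant.
- Fisher, 5/10 vs 0/10: p = 2·252/15504 = 0.033, significant. Power = P(X ≥ 5 | 10, 0.4) = 36.7%.
- Uncorrected chi-square, 3/10 vs 0/10: 20·30²/(10·10·3·17) = 3.53 < 3.84, not significant.
- Uncorrected chi-square, 4/10 vs 0/10: 20·40²/(10·10·4·16) = 5.0, significant. Power = P(X ≥ 4 | 10, 0.4) = 61.8%.

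So an observed result exactly equal to the planned difference, 4/10 vs 0/10, fails Fisher's test. So does 8/10 vs 4/10 (p = 0.17).

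**Exact power over all 40-point pairs** (sum of the binomial probabilities of all rejecting tables):

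| Evaluable per group | Two-sided test | Lowest (30% vs 70%) | 40% vs 80% | Highest (0% vs 40%, or 60% vs 100%) |
|---|---|---|---|---|
| 10 | Fisher | 24.3% | 25.3% | 36.7% |
| 10 | Chi-square, uncorrected | 41.8% | 42.5% | 61.8% |
| 12 | Fisher | 38.9% | 39.2% | 56.2% |
| 12 | Chi-square, uncorrected | 56.5% | 56.8% | 77.5% |

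The smallest n per group with 80% exact power is 16 (0% vs 40%), 27 (40% vs 80%) and 29 (30% vs 70%) for Fisher, and 13, 23 and 23 for uncorrected chi-square.

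**Which row applies.** With ten per group, each expected count is half the total fused or half the total not fused. All four reach 5 only when exactly 10 of the 20 patients are fused. In those tables both tests reject the same splits: 8 vs 2 is significant by both (chi-square 7.2; Fisher p = 0.023) and 7 vs 3 by neither (chi-square 3.2; Fisher p = 0.18). The protocol's chi-square-or-Fisher rule therefore has Fisher's power, 24–37%.

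**What ten per group can detect.** Two-sided Fisher reaches 80% power at differences of about 58 points (0% vs 58%) to about 68 points (16.5% vs 84.7%), depending on base rates. For example, 80% vs 12% gives 80.3%.

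**Attrition.** 10/(1 − 0.20) = 12.5, so 13 per group. Twelve is 10 × 1.2. With 20% loss, 12 × 0.8 = 9.6 remain; the loss that leaves ten is 2/12 = 16.7%.

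**The case against.** *Sidedness is not stated.* True. A one-sided uncorrected chi-square with ten per group reaches 83% at exactly 0% vs 40%. It falls to 72% at 5% vs 45% and is 61% at 40% vs 80%. At the one pair where it succeeds, the smaller expected counts are 2, so the protocol's own rule calls for Fisher, and one-sided Fisher reaches at most 62%. What stands is that the finding must be worded as two-sided.

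*The 40% may be relative.* This does not help: 80% vs 48% gives 15% (Fisher) and 28% (chi-square).

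*The expected difference may be larger than 40 points.* This is the strongest reply. The Background cites fusion of up to 80% after simple discectomy. If fusion after arthroplasty were 10% or 5% (an assumption; the document gives no rate), two-sided Fisher power with ten per group would be 84% or 93%. A reader might therefore go too far and infer that the trial cannot answer its fusion question. The document does not support that; it supports only that the stated detectable difference and the stated size do not match. If a larger difference was meant, the sample size section still needs correcting.

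*How the authors reached ten.* A reader might infer a one-sided unpooled formula. Several approximations fall near ten at the zero-fusion edge, and the document does not say which was used, if any.

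*Fusion stands in for the primary outcome.* A reader might add that power for a normal motion sequence must be lower still. The protocol discloses the surrogate and gives its reason, and any figure for the loss would rest on invented inputs. It is not part of this point.

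**Conclusion.** The statement is wrong as written. With ten evaluable patients per group and a true 40-point difference, the planned two-sided analysis has 24–37% power, less than half of the stated 80%. Even the uncorrected chi-square, which the protocol's small-cell rule would not use here, stays at 62% or below. Full retention of twelve per group does not reach 80% either.

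The result rests on three readings: two-sided testing, 40% as percentage points, and the tests as named in Statistical methods. It does not depend on the unstated fusion rates, because all pairs were scanned. The probable failure to reach significance is conditional on a true difference of 40 points. The attrition slip is real, but on its own it is minor, at most one patient per arm.

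**What to change.** Keep twelve per group and restate the figures in Sample size calculation:

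- Give the assumed fusion rate in each arm, the test and its sidedness.
- State that with ten evaluable per group, two-sided Fisher reaches 80% power only for a difference of about 58–68 percentage points depending on base rates (for example 80% vs 12%), and that power for a 40-point difference is 24–37%.
- Correct the attrition sentence: twelve per group allows for 16.7% loss; 20% would need 13.
- While there, correct the label in "the power (β) of 80" per cent, since power is 1 − β.

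In the Discussion, soften the expectation of a conclusion on the primary outcome, unless the larger expected difference is stated and supported.

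The cost is wording only. The stated power becomes less favourable; no extra patients and no change to the analysis are needed.

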### Patient allocation and blinding

Each patient is allocated to either arthroplasty or simple discectomy by randomly drawing an unmarked opaque sealed envelope from a non-sequential stack. Randomization is performed in a 1:1 ratio without a fixed block size. The patient is informed about the result of the randomisation at the first radiological examination moment, up to two days before surgery. The surgeon and other caregivers are not blinded. Assessment of the radiological data is not blinded, since absence or presence of a prosthesis is clearly visible. The clinical outcome data are collected by a blinded caregiver.

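### Twelve per group does not quite cover a 20% loss if ten completers are needed: a minor inflation error of one patient per group

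*Protocol article*

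**What the plan says.** The section Sample size calculation of the protocol article links three figures. For α of 0.05, 80% power and a 40% difference in the proportion of fused segments, "the necessary number of participants per group is ten". It then adds the allowance for attrition: "At a projected loss to follow up of 20% the amount of participants needed is twelve in each group". With three pilot patients, all given the prosthesis, it concludes: "The total number of patients that will be included is therefore 27". No inflation formula is shown, and the fusion rate expected in each group is not given. Patient allocation and blinding confirms equal allocation, and the Methods part of the Abstract repeats the 24 randomised patients.

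**The concern.** The article presents ten as the number the comparison needs, and the 20% as the share of enrolled patients expected to be lost. On that reading the enrolled number times 0.8 should be at least ten. For twelve it is not. Twelve per group sets the 24 randomised and the total of 27, so figures the trial relies on do not follow from the inputs printed beside them. What is at stake is whether the evaluable sample, and with it the claimed power, survives the attrition that the plan itself expects.

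**Working it through.** Inputs from Sample size calculation: 10 completers per group; 20% loss; 12 enrolled per group; 3 pilot patients; total 27; α = 0.05; a 40% difference in fusion. Allocation is 1:1 (Patient allocation and blinding). Assumptions of mine, because the article does not say: the test is two-sided, the 40% is an absolute difference, and the two fusion rates are varied over a range.

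1. **Reproducing the stated figure.** 10 × (1 + 0.20) = 12.0, which matches exactly. Rounding 10 / 0.8 = 12.5 down also gives 12. Then 12 + 12 + 3 = 27.

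2. **Applying the loss to the enrolled number.** 12 × (1 − 0.20) = 9.6 expected completers per group, 0.4 short of ten.

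3. **Solving for the enrolled number.** 10 / (1 − 0.20) = 12.5, rounded up to 13 per group. Check: 13 × 0.8 = 10.4. Randomised total 2 × 13 = 26; with the pilot, 26 + 3 = 29.

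4. **Loss that twelve does cover.** 1 − 10/12 = 16.7%, that is, two patients. A third loss (3/12 = 25%) leaves nine.

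5. **Cost in power.** Two-sided comparison of two proportions by normal approximation with pooled variance under the null, where Δ = p1 − p2 and p̄ is the mean of the two rates: power = Φ{[Δ√n − 1.96√(2p̄(1 − p̄))] / √(p1(1 − p1) + p2(1 − p2))}.
   - 40% vs 0%: 0.625 at n = 10, 0.605 at n = 9.6 (2.0 points).
   - 80% vs 40%: 0.442 at n = 10, 0.426 at n = 9.6 (1.6 points).
   - 70% vs 30%: 0.426 at n = 10, 0.411 at n = 9.6 (1.5 points).

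6. **The base figure, for context.** The powers in step 5 are already well below 80% at n = 10. The same two-sided formula solved for 80% power gives 15 per group (40% vs 0%) to 24 (70% vs 30%), and 23 at 80% vs 40%. Among the variants tried, ten is matched exactly only by a one-sided, unpooled formula at the extremes 40% vs 0% or 100% vs 60%.

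**The case against.** The case for leaving the figure alone is that the gap is of rounding size. Patients come in whole numbers: 20% of 12 is 2.4, and if two are lost exactly ten remain. With independent 20% loss, ten is the most likely number of completers in a group of twelve, and the chance of keeping at least ten is 0.56 (0.75 with thirteen). The Discussion also concedes that the sample is small. All of this stands, and it limits the size of the point. It does not make twelve follow from ten and 20%, because the expected number is still below the stated minimum.

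Three stronger readings are tempting and are not supported.

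- A reader might infer that the authors multiplied by 1.2. That reproduces twelve, but no formula is shown and rounding down would do the same.
- A reader might judge the plan by the chance that both groups keep at least ten: 0.56² = 0.31 with twelve and 0.75² = 0.56 with thirteen. The plan sets no such criterion. An allowance for loss normally targets the expected number, and thirteen would fail this criterion 44% of the time.
- A reader might take 29 as the right total. It is right only if ten is right, and step 6 of the working gives reason to doubt that.

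**Conclusion.** The statement is wrong as written, but the error is minor. Given ten completers and 20% loss among those enrolled, 13 per group are needed rather than 12. The shortfall is one enrolled patient per group, two in total, or 0.4 of an expected completer per group. The power cost of about 1.5 to 2 points rests on the normal approximation, a two-sided test and the fusion rates tried; the article fixes neither the sidedness nor the rates. A reader might infer that this slip leaves the trial materially underpowered. It does not: power at ten per group is already about 0.43 to 0.63 under the same assumptions, and one more patient per group would not repair that. Whether ten is the right base is a separate question, which this correction does not settle.

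**What to change.** Change one sentence in Sample size calculation. The simplest course is to keep 24 randomised and 27 in total, and to say that twelve per group allows for the loss of two patients per group (16.7%) while keeping ten. This costs no patients.

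If the 20% is to stay, say that, taking ten as given, it needs 13 per group: 26 randomised and 29 with the pilot. This costs two more patients, and the number in the Abstract must change with it.

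In either case, if power is restated, first give the fusion rate assumed in each group and whether the test is one- or two-sided, since no single power figure follows without them. If the base of ten is revised, divide the new figure by 0.8 and round up.
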